### Interim analyses {21b}

Formal interim analyses will be performed at completion of the 2-year, 5-year and 10-year visits. Results of these analyses will be used for dissemination of study results.

### Methods for additional analyses (e.g. subgroup analyses) {20b}

No additional subgroup analyses are planned.

### Methods in analysis to handle protocol non-adherence and any statistical methods to handle missing data {20c}

Non-adherence to randomisation will be analysed both as intention-to-treat and per-protocol. Missing data will be imputed according to instrument guidelines if necessary.

### Plans to give access to the full protocol, participant level-data and statistical code {31c}

The full protocol is presented here. Collected data will not be made available to the public. A lay summary of findings will be provided to the participants who requested this during the consenting process after completion of the study.

## Oversight and monitoring

### Composition of the coordinating centre and trial steering committee {5d}

The coordinating centre is North Shore Hospital, Takapuna, Auckland 0740, New Zealand. The trial steering committee includes the principal investigator, a research coordinator and research assistants involved with study coordination. The committee will meet on a monthly basis.

### Composition of the data monitoring committee, its role and reporting structure {21a}

A Data Safety Committee comprising of the principal investigator, a consultant orthopaedic surgeon independent of the study, a statistical advisor and a patient advocate will be formed to review the data and any adverse event forms.

### Adverse event reporting and harms {22}

All adverse events will be documented in an electronic site log. All serious adverse events will be documented on case report forms by the research assistant and reviewed by the primary investigator. Date of occurrence, description, severity, relationship to study device, treatment and date of resolution will be captured. The investigator will comply with the applicable regulatory requirements related to the reporting of serious unexpected adverse device reactions to the regulatory authority (MedSafe NZ) and the national ethics committee.

### Frequency and plans for auditing trial conduct {23}

There are no plans for formal auditing of trial conduct; however, there will be a yearly report of trial progress and protocol deviations to the national ethics committee.

### Plans for communicating important protocol amendments to relevant parties (e.g. trial participants, ethical committees) {25}

Amendments to the protocol will be reported to the national ethics committee, and an application for approval submitted if significant amendments need to be made. Amendments will be communicated to study participants as necessary.

## Dissemination plans {31a}

Findings from this study will be disseminated through peer-reviewed publications and conferences by the study investigators. A lay summary of the findings will be shared with participants at the completion of the study.

## Discussion

Fully cementless TKA components offer promising benefits such as bone stock preservation [9], avoidance of cement debris, decreased operating time [10] and improved biological fixation [11]. However, older designs have been associated with higher early revision rates due to lack of bony ingrowth, particularly for the tibial and patellar components [16, 17]. Newer highly porous metal designs introduced with the aim of improving biological fixation have shown promising survivorship [6, 14, 15] but randomised data is lacking for fully cemented (tibia, femur, patella) TKA.

Based on reports involving earlier designs of cementless TKA components, there is a chance that patients may be at risk of being treated with a component that may be deemed inferior after further analysis; however, there is nothing a priori to suggest this. Patients will be carefully monitored during the study and interim analyses are planned after 2 years to ensure patient safety.

## Trial status

Protocol version 1.2, May 2019. The study began recruiting in September 2017. Decision was made to complete recruitment in March 2020 as a result of the unexpected impact of COVID-19 lockdowns on elective surgery volumes. Last patient visit for this 5-year study is anticipated to be in 2025.

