**Methods:**

The Knee-Fix study is a two-arm, single-blinded, non-inferiority randomised controlled trial with 160 patients in each arm and follow-up at 6 weeks, 6 months, 12 months, 24 months, 5 years and 10 years. The primary outcome of interest is implant fixation, which will be measured by assessment of postoperative progressive radiolucencies with the Knee Society Total Knee Arthroplasty Roentgenographic Evaluation and Scoring System. Secondary outcome measures are patient-reported outcomes, measured using Oxford Knee Score (OKS), International Knee Society System (IKSS), Forgotten Joint Score-12 (FJS-12), EuroQol (EQ-5D-5L), VAS Pain, Patient Satisfaction Score and Net Promoter Score.

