### Outcomes {12}

The main reason for TKA failure is aseptic loosening; therefore, the primary outcome of interest is implant fixation, which will be measured by assessment of postoperative progressive radiolucencies. Standard anterior-posterior (AP) and medio-lateral (ML) X-rays of the study limb will be obtained pre-operatively and post-operatively at 6–12 weeks, and 2, 5 and 10 years post-operatively (Table 1). Radiographic assessment will be performed following the Knee Society Total Knee Arthroplasty Roentgenographic Evaluation and Scoring System [26], which will produce a single score for each component. All radiographs will be measured by one investigator to ensure consistency. The score at the 5-year follow-up will be the primary outcome of interest; however, the scores at other follow-ups will also be measured and presented.

**Table 1 Tab1:** Patient evaluation schedule for Knee-Fix study: an RCT evaluating cemented vs. cementless total knee arthroplasty

	Study period						
	Enrolment	Allocation	Post-allocation				Close-out
Timepoint	***−t***_***1***_ (−2 months)	0	***t***_***1***_ (6–12 weeks)	***t***_***2***_ (12 months)	***t***_***3***_ (24 months)	***t***_***4***_ (5 years)	***t***_***5***_ (10 years)

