### Sample size {14}

The main outcome measure is the incidence of radiolucencies using plain X-rays. To calculate sample size, we used a non-inferiority test; that is, the uncemented-fixation technique is acceptable if it is not worse than the standard cemented TKA technique based on the incidence of radiographic lucencies. Power calculations were based on estimates from a previous RCT, where 11% of cemented TKA and 2% of uncemented TKA were found to have progressive radiolucencies [21]. Using a power of 80%, 95% confidence level and a non-inferiority limit of 9%, 150 patients are needed in each group. An additional 10 patients per group (5%) will be recruited to allow for loss to follow-up, bringing the target to 160 patients per group (total of 320 patients). The estimated loss to follow-up of 5% is lower than other studies, however is based on previous experience of minimal loss to follow-up of our RCT patient cohorts [32]. Every individual in New Zealand accessing health systems is assigned a national unique health identifier, which allows for comprehensive capture of patient contact details, clinical notes and radiographs, including those who have moved to a different area.

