## Assignment of interventions: allocation

### Sequence generation {16a}

A block randomisation process will be used for this study. A central randomisation list will be computer generated by a consultant statistician at a 1:1 ratio. This method will ensure allocation of patients into the two groups with an equal sample size over time.

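### Recruitment closed in March 2020 for COVID-19 reasons, but 160 per arm and 80% power stand without the number enrolled or any reconciliation

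*Protocol article*

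**What the plan says.** The abstract's Methods paragraph describes a "non-inferiority randomised controlled trial with 160 patients in each arm", with no word marking this as a plan. Sample size {14} takes its rates from an earlier randomised trial in which "11% of cemented TKA and 2% of uncemented TKA were found to have progressive radiolucencies". It then states: "Using a power of 80%, 95% confidence level and a non-inferiority limit of 9%, 150 patients are needed in each group". On attrition it adds: "An additional 10 patients per group (5%) will be recruited to allow for loss to follow-up". This gives a target of 160 per group, 320 in all. Sequence generation {16a} fixes 1:1 allocation, and Outcomes {12} sets the primary time point: "The score at the 5-year follow-up will be the primary outcome of interest".

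Trial status gives the protocol version as 1.2 of May 2019 and the start of recruitment as September 2017. It then reports: "Decision was made to complete recruitment in March 2020 as a result of the unexpected impact of COVID-19 lockdowns on elective surgery volumes". It gives no number randomised. No section gives a revised target or a revised power.

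Statistical methods {20a} compares the proportions scoring 4 or above, compartment by compartment, with Fisher's exact test and a 0.05 significance threshold. It does not compare anything with the 9-point limit.

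**The concern.** The size and power were set in a version that predates the closure. The article reports the closure but leaves those figures as they were. A trial that stops because operating lists have shrunk has usually not reached its target, and this article does not say that it had.

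The limit is fixed at 9 points, so fewer patients mean a wider interval against the same limit. A 5-year result that fails to exclude 9 points could then come from limited accrual rather than from worse fixation. Fewer patients also make a non-significant Fisher test more likely, and in a trial framed as non-inferiority that is easily misread as showing the uncemented implant to be no worse. Readers would judge either result against 160 per arm and 80% power, which the trial may not have.

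**Working it through.** **Inputs.** From Sample size {14}: 11% event rate in the cemented arm, 9-point limit, 80% power, 95% confidence level (sidedness not stated), 150 evaluable per arm, 5% loss, target 160 per arm. From Trial status: closure in March 2020, number enrolled not given.

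**Reproducing the plan's figure.** With the same true rate p in both arms and limit d,

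n per arm = 2p(1 − p)(z₁₋α + z₀.₈₀)² / d².

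For p = 0.11, d = 0.09 and one-sided α = 0.05:

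2 × 0.11 × 0.89 × (1.645 + 0.842)² / 0.09² ≈ 149.5, rounded up to 150.

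This matches. One-sided 2.5% gives 190. Non-inferiority with true rates of 11% and 2% gives 23 (one-sided 5%) or 29 (one-sided 2.5%). The plan's 80% therefore rests on equal true rates of 11% and one-sided 5%.

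**Slack.** 150 / 0.95 = 157.9, so 158 enrolled per arm are needed at the stated loss. The target of 160 leaves 2 per arm spare. The 10 extra patients are 10/160 = 6.25% of the target; if all 10 were lost, exactly 150 would remain.

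**Power at smaller enrolments.** With evaluable n = 0.95 × enrolled,

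power = Φ(0.09 / √(2 × 0.11 × 0.89 / n) − 1.645).

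For 120 enrolled, n = 114: the standard error is √(0.1958/114) = 0.0414, 0.09/0.0414 = 2.172, and Φ(2.172 − 1.645) = 70.1%. The 90% interval is the two-sided interval that matches one-sided 5%; its half-width is 1.645 × standard error. Enrolments below 160 are assumed values, because the document gives none.

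| Enrolled per arm | Evaluable per arm | Power | 90% half-width (points) |
|---|---|---|---|
| 160 | 152.0 | 80.6% | 5.9 |
| 157 | 149.2 | 79.9% | |
| 150 | 142.5 | 78.3% | |
| 140 | 133.0 | 75.8% | |
| 130 | 123.5 | 73.1% | |
| 120 | 114.0 | 70.1% | 6.8 |
| 100 | 95.0 | 63.2% | 7.5 |

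**Sensitivity to sidedness.** If the 95% confidence level means one-sided 2.5%, enrolments of 160, 120 and 100 per arm give 70.8%, 58.4% and 50.9%.

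**The case against.** The strongest reply is that nothing here is a contradiction. Sample size {14} records a design calculation and calls 160 a target. That calculation reproduces and remains correct as the plan. Trial status is a later update of a different kind, and the number randomised is normally reported with the results. Completing recruitment could even mean that the target was met. Much of this stands: the 80% is a valid design figure and should not be overwritten, and the shortfall is inferred. What does not stand is that no clarification is due. The article itself prints a closure for a reason unrelated to sample size, next to an abstract that gives 160 per arm without calling it planned.

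A reader might infer that the trial is underpowered, or by how much. The document does not support that. With no enrolment figure the loss may be nil, small or large, and the table shows only what each assumed number would imply.

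A reader might also set two-sided 95% half-widths (7.0, 8.1 and 8.9 points at 160, 120 and 100 enrolled) against these powers and conclude that at 100 per arm the half-width nearly equals the limit. That mixes two error rates. On the one-sided 5% basis of the powers, the half-width at 100 is 7.5 points.

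It can also be said that accrual matters little if the uncemented implant is truly better. This is correct: with true rates of 11% and 2%, non-inferiority power is 99.7% at 80 evaluable per arm, even at one-sided 2.5%. But the plan's 150 per arm does not rest on that case, so its 80% cannot be defended by it.

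Finally, a non-significant Fisher test can be misread at full enrolment too. That is so. A shortfall makes the misreading more likely but does not create it.

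**Conclusion.** The point holds as a failure to reconcile stated figures. The article gives an external reason for closing recruitment, does not say that 320 was reached, and leaves 160 per arm and 80% power without an achieved number beside them. Early closure is the likely reading but is not established.

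Under equal true rates of 11%, a 9-point limit, one-sided 5% and 5% loss, power drops below 80% once 157 or fewer per arm were enrolled. It stays above 75% at 140 and is about 70% at 120 and 63% at 100. If the target was met, there is no power loss and Trial status needs only one sentence. The one-sided 5% is inferred from the reproduced 150 and is not stated in the protocol. Confidence is medium because the deciding number is absent. The correction is worth making before the 5-year analysis, since recruitment is closed and the sponsor already holds that number.

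**What to change.** - **Abstract and Sample size {14}:** label 160 per arm and 80% power as planned figures. Leave the calculation and the 9-point limit as they are.
- **Trial status:** state the number randomised per arm at the March 2020 closure. If it is below 158, give the power at that number under the original assumptions, beside the planned 80% and not in place of it. If 320 was reached, say so.
- **Statistical methods {20a}:** state that non-inferiority will be judged by whether the confidence interval for the difference in proportions (uncemented minus cemented) excludes 9 points, and give the interval's level. State that a non-significant Fisher test, or an interval containing both 0 and 9 points, will not be reported as non-inferiority. An interval wholly above 0 that still contains 9 fails the same criterion.

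The cost is a few sentences and one recalculation from a number already held. The downside is a possibly less favourable stated power. No further enrolment is proposed.

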## Data Availability

Identifiable data will only be made available to the investigators of the trial. Deidentified data can be shared upon request.

## Abbreviations

ANOVA: Analysis of variance
AP: Anterior-posterior
EQ-5D-5L: EuroQol 5 Dimension
FJS-12: Forgotten Joint Score-12
GCP: Good Clinical Practice
IKSS: International Knee Society System
ML: Medio-lateral
OKS: Oxford Knee Score
TKA: Total knee arthroplasty
VAS: Visual Analog Scale
